# Assessment of a new unidirectional barbed suture versus a conventional suture for anastomosis during robotic-assisted Roux-en-Y gastric bypass surgery in obese patients: BARGASTRO — study protocol for a German randomized active-controlled trial

**DOI:** 10.1186/s13063-025-09401-9

**Published:** 2026-01-06

**Keywords:** Barbed suture, Bariatric surgery, Anastomosis, Robotic-assisted surgery, Roux-en-Y gastric bypass, Complications, Suturing time, Obesity

## Abstract

**Background:**

Gastric bypass surgery is an efficient surgical intervention for the treatment of obese patients. The procedure can be performed either laparoscopically or robotic assisted. To simplify the intracorporeal handling of the suture material in a bi- or tri-dimensional plane, a new generation of sutures, named barbed sutures, has been developed recently and is being used for different indications. Barbed sutures allow knotless slippage-resistant suturing due to the self-anchoring elements distributed along the thread length and therefore obviate the need for assistance. Their safety and efficacy have been demonstrated in several meta-analyses and systematic reviews. In the present study, the clinical performance of a new unidirectional barbed suture material, which differs in regard to its configuration from other barbed suture materials, is analysed and compared to a conventional suture material in robotic-assisted gastric bypass surgery to treat morbid obesity.

**Methods:**

The study will be performed as an industry-sponsored, mono-centre, randomized, active-controlled, two-arm, parallel-group, superiority trial. A total of 150 patients will be randomly allocated to both suture types in a 1:1 ratio. The suture material will be used to construct the gastro-jejunal anastomosis as well as the jejuno-jejunal anastomosis. The time needed to create both anastomoses is the primary endpoint. Intraoperative handling of both suture materials, patient satisfaction, pain, and complications occurring during the study will serve as secondary outcomes. Furthermore, the difference in quality of life using two different questionnaires (EQ5D5L and Bariatric Analysis and Reporting Outcome System (BAROS)) will be assessed preoperatively and postoperatively (30 days and 12 months) and will be compared between the suture groups as well as over time. The EQ-5D-5L questionnaire consists of five dimensions (mobility, self-care, usual activities, pain or discomfort, anxiety or depression) and a visual analogue scale (VAS) to record the patient’s health status. The BAROS evaluates three sub-categories: The percentage of excess weight loss, the changes in medical conditions, and quality of life, leading to three individual sub-scores, which are added to the final total score defining the failure or success of treatment. The follow-up period is 1 year after surgery.

**Discussion:**

To our knowledge, the BARGASTRO study will be the largest randomized controlled trial investigating a barbed suture versus a conventional one in robotic-assisted gastric bypass surgery to treat obese patients. The study will provide and report clinical data on evidence level Ib.

**Trial registration:**

NCT05433688. Registered on 12 Oct. 2022

## Administrative information

Note: The numbers in curly brackets in this protocol refer to SPIRIT checklist item numbers. The order of the items has been modified to group similar items (see http://www.equator-network.org/reporting-guidelines/spirit-2013-statement-defining-standard-protocol-items-for-clinical-trials/).

## Introduction

### Background and rationale {6a}

Laparoscopic gastric surgery (LGS) is the standard surgical treatment for gastric cancer and obese patients [1]. Known short-term complications after LGS are anastomosis leakage, bleeding, or obstruction, which may lead to ileus or peritonitis requiring a re-intervention, causing a longer hospital stay. Therefore, a secure creation of an intestinal anastomosis is of major importance. Different devices, such as staplers or suture materials applied either in the interrupted or continuous suture technique, are currently in use to create an anastomosis [2, 3].

In laparoscopic surgeries, lengthened surgical times are mainly due to three factors: first, the difficulty of working in a bidimensional plane; second, the identification of the surgical planes; and, third, the handling of intracorporeal and extracorporeal sutures. The latter is being the most difficult for surgeons in training when the whole procedure must be achieved by taking the laparoscopic approach [2–5]. Barbed sutures have been reported in the literature to greatly facilitate the suturing during different laparoscopic procedures compared to traditional sutures [6–9].

Barbed sutures are available as absorbable (mid-term and long term) as well as non-absorbable monofilament sutures. The barbs are either arranged in a unidirectional or bidirectional configuration and allow knotless slippage-resistant suturing due to the self-anchoring elements distributed along the suture length, which penetrate the tissue and lock the suture in place [10]. By eliminating knots, there is an inherent reduction in inflammation due to the reduction of foreign material at the wound site [11–13]. This type of suture is nowadays frequently used in gynaecological, urological, orthopaedic, and aesthetic surgical procedures [14–20]. Studies comparing barbed threads versus traditional suture material have shown equivalence regarding performance, safety, and tensile strength [15, 20]. The benefits of barbed sutures are the easy usage and the speed of placement [11, 13]. In addition, this type of suture material provides a uniform tension along the closure line and multilayer closure is possible [21, 22]. Barbed sutures obviate the need for assistance and lead to increased suture efficiency, especially with tissue under tension. The suture material has the potential for less scarring [23], reducing blood loss and surgical time, and knot complications can be avoided [6, 7, 13].

Several studies exist that compare barbed sutures to traditional sutures for the construction of intestinal anastomosis during laparoscopic gastric surgery [6–9]. De Blasi and co-workers observed a reduced anastomosis suturing time and a decrease of operation costs in patients undergoing a laparoscopic Roux-en-Y bypass surgery compared to traditional sutures without an increase in the complication rate [24]. Similar findings were reported by Gys et al., Milone et al., and Constantino et al. [25–27]. The usage of barbed suture for laparoscopic RYGB revealed a faster enterotomy closure, lower costs, a similar complication rate, and no difference in overall operation duration in comparison to conventional sutures. The outcome of the literature showed that barbed sutures are safe and effective for wound closure with a comparable complication rate, which indicates that their performance is at least equivalent to conventional sutures for soft tissue approximation [6–9].

Currently, less clinical evidence is available regarding the role of barbed sutures used for anastomosis formation during robotic-assisted bariatric surgery, notwithstanding their usage is already widespread in this surgical intervention. In the authors’ view, barbed sutures have great advantages especially in robotic bariatric surgery, because in contrast to laparoscopic settings no assistance has to control, pull, and tighten the thread regularly, which simplifies the handling and construction of the anastomosis.

At the time, when the study protocol was prepared for the present study, a total of 14 clinical studies had been performed prospectively or retrospectively, either comparing conventional suture materials to barbed sutures [24–26] or reporting the outcome of barbed sutures [17, 28–36] for the construction of intestinal anastomosis during laparoscopic gastric surgery using either unidirectional or bidirectional mid-term or long-term barbed sutures. To our knowledge, the current RCT “BARGASTRO” will enrol the highest number of patients ever systematically analysed and published in robotic-assisted gastric bypass surgery. Furthermore, it will provide clinical data on evidence level Ib, due to its design. The present industry-initiated study is performed after the CE-mark of the suture material, and the participating hospital is the first user of the new unidirectional barbed suture in general surgery.

### Objectives {7}

The study aims to show the superiority of a new barbed suture over a conventional suture material regarding the suturing time needed to perform the gastro-jejunal (GJA) and jejuno-jejunal anastomosis (JJA) after robotic-assisted Roux-en-Y gastric bypass surgery (RYGB) in bariatric patients, without an increase in the complication rate.

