#### Secondary outcomes

The rate of anastomosis leaks, anastomosis stenosis, gastric fistula, obstruction, anastomosis bleeding and re-anastomosis, and the frequency of other complications according to Clavien–Dindo will be collected as safety variables until discharge, 30 days, and 12 months postoperatively [38].

In addition, the operation duration, costs, length of hospital stay, patient satisfaction, pain, and quality of life will be compared in both suture groups and over time.

Length of hospital stay is defined as the period from day of surgery until day of discharge. Cost assessment includes the costs of suture material, costs per operation minute, number of used threads, and costs per hospital day. Pain evaluation will be performed by the patient using the visual analogue scale (VAS), which is a numeric scale ranging from 0 (no pain) to 100 (maximal pain). In addition, patients will be asked by the surgeon for their postoperative satisfaction using a numeric scale from 0 (not satisfied) to 100 (maximal satisfaction). Quality of life will be analysed using the EQ-5D-5L questionnaire, which is a standardized measure of health status developed by the EuroQol Group to provide a simple, generic measure of health for clinical and economic appraisal [39]. The questionnaire consists of a descriptive system comprising five dimensions (mobility, self-care, usual activities, pain or discomfort, anxiety, or depression) and the EQ visual analogue scale (EQ-VAS). Each dimension has five levels: 1 = no problem, 2 = slight problems, 3 = moderate problems, 4 = severe problems, and 5 = extreme problems. The result of the assessment of all five dimensions leads to the so-called EQ index, which ranges from 1 minimum to 5 maximum. Using the EQ-VAS, each patient records his/her healthy status ranging from 0 (the worst health you can imagine) to 100 (best health you can imagine). The EQ5D5L is used in the German language, and a licence has been obtained by the sponsor from EuroQol–Group. 

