### Sample size {14}

The sample size calculation is based on the primary endpoint “time to perform the GJA and JJA” to show superiority of a unidirectional barbed suture compared to a conventional suture material. Several studies have been published analysing both types of suture materials regarding this outcome parameter [6, 7]. The weighted group means and the weighted pooled standard deviations were calculated based on the results of the subset of four studies [24–27] providing suturing times to create the GJA. Considering 14.20 min to approximate the GJA in the barbed suture group compared to 16.10 min in the conventional group, a sample size of 71 patients in each suture group will have 80% power to detect a mean difference of −1.90 min assuming that the common standard deviation is 4.00 using a two-sample *t*-test with a 0.05 two-sided significance level. Including a drop-out rate of 5%, the sample size becomes up to 75 patients in each suture group, a total of 150 patients. The times to create the JJA are only reported in two studies [25, 27] with great differences. Therefore, to calculate the sample size for the current study, the time for the construction of the JJA was not taken into account. In addition, it was previously mentioned that the times for JJA formation did not differ between traditional and barbed sutures [6]. For sample size calculation, nQuery Advisor^®^7.0 was used.

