## Statistical methods

### Statistical methods for primary and secondary outcomes {20a}

The intention-to-treat principle will be applied for data analysis. A CONSORT diagram will be utilized to graphically display the eligibility, allocation, and follow-up course of the participants (**41**). Demographics, anamnesis, and baseline characteristics will be presented in a tabular form by treatment group. Continuous measures will be summarized by the number of non-missing observations, minimum, maximum, median, and mean with standard deviation, and categorical measures by absolute and relative frequencies.

The primary outcome measure is the suturing time to perform the GJA and JJA. The independent samples *t*-test with a two-sided significance level of 0.05 will be used for the comparison of treatment groups (UBS vs. CS). 95% CI will be provided to allow a quantitative evaluation of the treatment effect with respect to the minimum clinically relevant difference of 1.9 min. The secondary variables will be analysed descriptively.

The test regarding the primary variable is considered confirmatory; all other tests are explanatory. For the analysis of binary data, a chi-square test will be used; for nonparametric data, a *U*-test according to Wilcoxon–Mann–Whitney or to Kruskal–Wallis will be used; and a *t*-test or one-way ANOVA will be used for metric data, if a normal distribution is assumed. All statistical tests will be performed two-tailed with a pre-specified significance level of *α* = 5%. Two-sided 95% confidence intervals will be given, where appropriate.

The secondary outcomes include the following:
Pain (visual analogue scale, values from 0 to 100, 100—max. pain)Satisfaction (numeric scale values from 0 to 100, 100—best)EQ-5D-5L questionnaire: EQ index range from 1 best to 5 worse and EQ-VAS scale value (0–100—best).BAROS questionnaire, three sub-scores with a maximum of 3 points each (weight loss (% of excess), improvement of medical conditions and Quality of Life), and the total score with a maximum of 9 points (best).Length of hospital stay in daysHandling assessment of the suture material (different dimensions using a Likert scale with levels from 1 excellent to 5 worse).

The outcomes will be analysed descriptively and compared between suture groups and between visits, where appropriate.

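### The aim promises faster suturing with no increase in complications, but the plan can only estimate the complication difference, and with wide uncertainty

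*Protocol article*

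**What the plan says.** The Objectives section {7} sets the aim as superiority of the barbed suture (UBS) over the conventional suture (CS) in suturing time for the two anastomoses "in bariatric patients, without an increase in the complication rate".

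Under Outcomes {12}, the secondary outcomes include "The rate of anastomosis leaks, anastomosis stenosis, gastric fistula, obstruction, anastomosis bleeding and re-anastomosis", together with other complications graded by Clavien–Dindo. These "will be collected as safety variables until discharge, 30 days, and 12 months postoperatively".

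Section {20a} on statistical methods has four sentences that bear on their analysis:
- "The secondary variables will be analysed descriptively".
- "For the analysis of binary data, a chi-square test will be used".
- "The test regarding the primary variable is considered confirmatory; all other tests are explanatory".
- "Two-sided 95% confidence intervals will be given, where appropriate".

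The sample size section {14} uses the gastro-jejunal suturing time only (difference 1.90 min, SD 4.00 min, "0.05 two-sided significance level", 80% power). No section states an expected complication rate, a largest acceptable increase or a rule for concluding that complications have not increased. The Discussion says only that complication rates in minimally invasive bariatric surgery are low.

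**The concern.** The clause in the objective is a statement of no harm. A test of difference can reveal an increase, but failing to find one is not evidence that none exists, least of all when events are few. The objective is therefore worded more strongly than the analysis behind it.

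The stakes are real. The background section reports an earlier laparoscopic suture study in almost the same words, and infers at least equivalent performance from comparable complication rates in the literature. It also says that the hospital is the first user of this suture in general surgery and that the trial will supply level Ib evidence. A report that the suture is faster with no more complications would carry weight, and its second half would be unsupported.

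**Working it through.** **1. The plan's own figure.** Inputs from section {14}: difference 1.90 min, SD 4.00 min, two-sided alpha 0.05, power 80%.
- Normal approximation: n = 2 × (1.960 + 0.842)² × 4.00² / 1.90² = 69.6, so 70 per arm.
- Two-sample t-test (noncentral t): n = 70.5, so 71 per arm, with power 80.3% at 71.
- Drop-out of 5%: 71 / 0.95 = 74.7, so 75 per arm and 150 in total.

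The stated size reproduces. Complications play no part in it.

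**2. Power of the chi-square test for complications.** n = 75 per arm and two-sided alpha 0.05 come from the article. Control rates are assumptions over a range of 1% to 10%. Method: enumerate all pairs of binomial counts (i, j) and sum the probabilities of the pairs with |i − j|/n divided by √(2p̄(1 − p̄)/n) above 1.96, where p̄ = (i + j)/(2n).

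| CS rate → UBS rate | Power |
|---|---|
| 1% → 2% | 3% |
| 2% → 4% | 9% |
| 3% → 6% | 13% |
| 5% → 10% | 22% |
| 10% → 20% | 41% |

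Throughout this range, a non-significant result is more likely than not even if the rate doubles. By the normal approximation, 80% power would require the UBS rate to reach about 14.5% from 2%, 20% from 5% or 28% from 10%.

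**3. Precision of the estimate.** Newcombe's interval for p₁ − p₂ combines the Wilson limits (l, u) of each arm. Its upper limit is (p₁ − p₂) + √[(u₁ − p₁)² + (p₂ − l₂)²].
- 0/75 versus 0/75: the Wilson upper limit is 3.84 / (75 + 3.84) = 0.0487 and the lower limit is 0. The interval is ±4.9 points.
- 2/75 versus 2/75: ±6.8 points.
- 4/75 versus 4/75: p = 0.0533 with Wilson limits 0.0209 and 0.1293. √(0.0759² + 0.0324²) = 0.0826, so ±8.3 points.

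Even identical counts leave increases of about 5 to 8 points compatible with the data.

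**4. An illustration.** Take 6 UBS events against 1 CS event. Then p̄ = 7/150 = 0.0467, the standard error is √(0.0467 × 0.9533 × 2/75) = 0.0344, and z = (5/75)/0.0344 = 1.94, so p is about 0.053. The test does not reject, yet the Newcombe upper limit is about +15 points.

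**5. What a formal no-increase comparison would need.** With equal true rates p, margin m, one-sided 0.025 and 80% power, n = (1.960 + 0.842)² × 2p(1 − p) / m².
- p = 5%, m = 5 points: 7.85 × 0.095 / 0.0025 gives 299 per arm.
- p = 2%, m = 5 points: 124 per arm.
- p = 1%, m = 5 points: 63 per arm.
- p = 5%, m = 10 points: 75 per arm.

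Whether 75 per arm is enough therefore depends on a rate and a margin that the article does not give.

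**The case against.** The best defence is that this is a superiority trial with time as its only confirmatory endpoint. The clause about complications is a qualifier and not a second hypothesis, and exploratory safety analysis is normal in a trial of this kind. That largely stands. No non-inferiority hypothesis is announced, so the absence of a margin is not in itself a defect. The fault is narrower: a clause worded as something to be shown is paired with an analysis that cannot show it.

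A reader might go further in four ways that the article does not support:
- *A non-significant chi-square result will count as meeting the objective.* No section says so, and section {20a} labels every non-primary test as not confirmatory. The risk comes from the wording of the aim, not from a stated rule.
- *The chi-square test is the only tool.* Section {20a} also offers 95% confidence intervals. They are the right tool, but there is no limit to judge them against.
- *Complications were left out of the analysis.* They do not appear in the list in section {20a}, but they are named under Outcomes {12}. That list also leaves out operation duration and costs, so it looks abbreviated.
- *75 per arm can never support such a claim.* A 5-point margin at a 1% rate would have 87% power, and a 10-point margin at a 5% rate would have 80%.

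Two further points are fair. The event rates used here are assumed, and because all Clavien–Dindo complications are collected, the overall rate may not be low. Even at 10%, power for a doubling is only 41%. An unseen analysis plan may also fix the interval method and tables, so their absence from the article is not held against it. It would not change the wording of this objective or the basis of the sample size.

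**Conclusion.** The concern holds as a mismatch between the objective and the analysis. The clause on complications cannot be established by the analysis described, because absence of a significant difference is not absence of an increase and no acceptable limit is defined. Under assumed control rates of 2%, 5% and 10% with all 75 patients per arm analysed, a doubling would go undetected about 91%, 78% and 59% of the time. With four or fewer events in each arm and equal counts, the upper confidence limit would lie between about 4.9 and 8.3 points. The logical point does not depend on the assumed rates, but these sizes do. The primary comparison, its sample size and the data collection are unaffected.

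**What to change.** Restate the objective as superiority in suturing time, with complications described and compared by estimation. For each anastomotic complication named under Outcomes {12}, and for a composite of them, report the UBS minus CS risk difference with a 95% confidence interval (Newcombe, for example) at 30 days and 12 months. State in advance that any safety conclusion will quote the upper confidence limit and that p>0.05 will not be reported as no increase.

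This needs a change of wording and one extra table, with no additional patients, visits or data. The price is a more modest safety claim.

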### Trial design {8}

The BARGASTRO study is designed as a prospective, monocentric, randomized, two-arm parallel, active-controlled, superiority trial to compare a new unidirectional mid-term absorbable barbed (UBS) versus an absorbable traditional suture material (CS). A total of 150 patients are enrolled in one German clinic and randomly allocated in a 1:1 ratio to both suture groups. The surgical technique to create the gastro-jejunal as well as the jejuno-jejunal anastomosis will be standardized in both suture groups, and the participating surgeons are trained on the used suture technique. Patients will be kept unaware of the allocation (single blinded) until the completion of the study. After surgery, each subject will be examined on the day of discharge, 30 days, and 12 months postoperatively onsite at the hospital by surgeons performing the surgical procedure. This scheduled time has been selected because it represents the clinical routine setting of the participating hospital. Registration of the study has been performed in the platform for international clinical trials of the World Health Organization under http://www.clinicaltrials.gov NCT05433688 on 12 Oct. 2022. The local medical ethics committee responsible for the participating clinic approved the study on 15 March 2022 under project number D530/21. Our trial is reported in accordance with the SPIRIT guideline, which is a standard to publish study protocols [37]. The SPIRIT checklist is provided as an appendix, and a study flow chart is also included (Fig. 1).

